### Potential mechanisms

#### Mindfulness

Based on a review of mindfulness measures [82], we decided to use The Mindfulness Attention and Awareness Scale (MAAS [83]). MAAS is comprised of 15 items that measure mindfulness as a trait and five items that measure mindfulness as a state. In our study, only the trait items will be used (e.g., “*I could be experiencing some emotion and not be conscious of it until some time later*”), which are answered on a 6-point scale ranging from 1 (almost always) to 6 (almost never). The Cronbach’s alpha in the validation study was .87 [83].

#### Work-related maladaptive thinking patterns

Work-related maladaptive thinking patterns will be measured using the Work-Related Maladaptive Thinking Patterns Questionnaire [84]. The questionnaire is formative in nature and consists of 15 items. Each item refers to one cognitive distortion that can arise in the work context (e.g., unfair comparisons: “*My colleagues are faster and more skillful than me*”). Participants are asked to indicate how likely it is for them to think in the same way as described in the items, to which they respond using a 7-point scale from 1 (extremely unlikely) to 7 (extremely likely). The questionnaire has previously exhibited great internal consistency, ranging from .86 to .87 [84].

### Potential moderators and control variables

#### Supervisor support for recovery

Supervisor support for recovery will be measured using the 6-item Supervisor Support for Recovery Scale [35]. The scale was originally designed to be filled out by the supervisor. However, we will adapt the items so they can be answered by the employee, shifting the emphasis to the employee’s perception of the supervisor’s support for recovery (e.g., instead of “*I expect my subordinates to be willing to work around the clock, if necessary”*, this version will be used: “*My immediate supervisor expects his/her subordinates to be willing to work around the clock, if necessary”*). All responses are made on a 5-point scale from 1 (strongly disagree) to 5 (strongly agree). In the validation study, the scale has exhibited great internal consistency (α = .90 [35]).

#### Work-home segmentation supplies

Participants will also be asked to complete the 4-item Segmentation supplies scale developed by Kreiner [36]. All items are answered using a 7-point agreement scale from 1 (strongly disagree) to 7 (strongly agree), with 4 being neutral. An example item is: “*My workplace lets people forget about work when they’re at home*”. The scale has great internal consistency (α = .94 [36]).

#### Unfinished tasks

Unfinished tasks will be measured with items developed by Syrek, Weigelt, Peifer, and Antoni [37]. While the original version of the scale consists of 6 items, we will use a shorter 3-item version based on our previous work [85]. An example item is: “*I do not even start with important tasks I want to fulfill*”. The response scale ranges from 1 (strongly disagree) to 5 (strongly agree). The 3-item version has great internal consistency, with Cronbach’s α = .88 [85].

#### Time pressure

Lastly, time pressure will be measured using the adapted version of the ISTA (Instrument for stress-related job analysis) “time pressure” subscale [86, 87]. The subscale is comprised of 3 items (e.g., “*I was pressed for time*”), answered on a 5-point agreement scale ranging from 1 (strongly disagree) to 5 (strongly agree). The scale has previously shown acceptable internal consistency (α = .83 [86]).

#### Background variables

In the pre-screening questionnaire, participants will be asked to provide some basic demographic data (i.e., gender, age, the highest level of formal education and family status), basic information regarding their work (i.e., employment status, type of work, weekly working hours, tenure, leadership status and whether they are currently on sick leave) as well as some intervention-related data (i.e., willingness to dedicate enough time to the intervention, access to the internet, self-rated competency to use a computer, involvement in other forms of psychotherapy/psychoeducation, prescription of drugs to treat mental illnesses and the presence of a mental illness diagnosis).

In the questionnaire that will be administered at T2 (directly after the intervention), they will additionally be asked to report any significant work- (e.g., switching jobs), private life- (e.g., switching apartments), or intervention-related (e.g., participating in other interventions, aimed at improving mental health) changes during the last 6 weeks. They will also be asked to rate their overall satisfaction with the intervention, their attitudes towards the exercises, their previous experience with similar exercises, and their self-reported adherence to the intervention procedure.

### Statistical analysis

#### Sample size calculation

The G*Power 3.1 software was used to determine the minimum number of participants that need to be recruited [64]. We set the expected effect size to medium (*f(V)* = .25), the probability of a Type I error to α = .05, the statistical power (1-β) to .95 and chose a two-way repeated measures MANOVA (multivariate analysis of variance) with time (3 levels: pre, post, and follow-up) as the within-subjects factor and group (3 levels: CBT, MBSR, and control) as the between-subjects factor as the main statistical test. Given these specifications, the required total sample size is 151 participants (approximately 50 participants per group). In case of non-adherence and/or drop-out, the total sample size of 98 participants (approximately 33 participants per group) suffice with a more standard power level of .80.

#### Effect evaluation

The analyses will be carried out with SPSS [88] and Mplus [89]. The significance level used in the analyses will be .05. The main research questions (i.e., group differences in psychological detachment from work and burnout) will be analyzed with two separate two-way repeated measures analyses of variance (ANOVAs), with time as the within-subjects factor (3 levels: pre, post, follow-up) and group as the between-subjects factor (3 levels: CBT, MBSR, control), for each of the main outcomes separately. Significant interactions will be followed up with a simple effects’ analysis, using the Bonferroni correction to adjust for multiple testing.

The effects of the intervention on the secondary outcomes (i.e., general and work-related well-being) will be analyzed with a two-way repeated-measures MANOVA, with time as the within-subjects factor and group as the between-subjects factor. This analysis is contingent upon moderate correlations between the dependent variables [90]. Therefore, we will first examine correlations between the secondary outcome variables. Significant interaction effects will be followed-up with ANOVAs for each of the dependent variables and a discriminant descriptive analysis to further examine the effects. The moderation (i.e., supervisor support for recovery, work-home integration supplies, unfinished tasks, time pressure) and mediation (i.e., mindfulness, work-related maladaptive thinking patterns) effects will be analyzed using the PROCESS macro for SPSS [91]. T2 measures of the studied mediators will be utilized in these analyses. In order to explore both; the inter-individual variability and the intra-individual patterns of change trajectories in the mechanisms and the main outcomes during interventions, growth curve analyses will be conducted using data from the weekly questionnaires.

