### Work-specific outcomes

#### Burnout

Burnout will be measured using the Maslach Burnout Inventory - General Survey [71], which consists of 16 items that measure three burnout dimensions – professional efficacy (e.g., “*I can effectively solve the problems that arise in my work*”), exhaustion (e.g., “*I feel emotionally drained from my work*”) and cynicism (e.g., “*I’ve become less interested in my work since I started this job*”). All items are answered on a 7-point Likert scale from 0 (never) to 6 (every day). The professional efficacy (α = .71), cynicism (α = .79) and emotional exhaustion (α = .90) subscales all show satisfactory internal consistency [71].

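### Two primary outcomes are each tested at .05 with no correction between them, so the chance of at least one false primary interaction is up to 9.75%, and the burnout score entering its test is not named

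*Protocol article*

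**What the plan says.** All references are to the protocol article; the SAP is not available.

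- Objectives and hypotheses, and Measures, both give psychological detachment and burnout as primary outcomes.
- Effect evaluation sets the level: "The significance level used in the analyses will be .05". It plans two repeated measures ANOVAs, one per primary outcome, with three groups and three times. Bonferroni is attached only to the simple effects examined after a significant interaction.
- Sample size calculation uses the same undivided level: "the probability of a Type I error to α = .05, the statistical power (1-β) to .95". It gives "the required total sample size is 151 participants (approximately 50 participants per group"), and a drop-out fallback of 98 in total at power .80.
- The Burnout section describes the Maslach Burnout Inventory - General Survey, "which consists of 16 items that measure three burnout dimensions": professional efficacy, exhaustion and cynicism. Each has its own reliability. No total score is described and no lead subscale is chosen. By contrast, the sections on sleep quality and work engagement each describe an overall score.

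**The concern.** There are two routes to a positive primary result, and each carries the full .05. The article has no requirement that both outcomes be significant, no testing order and no split of alpha. The only multiplicity correction works inside one ANOVA, after its interaction is already significant, so it does nothing for the error rate across the two interaction tests. A reader who takes .05 as the trial's primary error rate will be misled.

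The burnout outcome adds to the problem. A correction across two tests means something only if there are exactly two tests. The analysis section counts one burnout ANOVA, but the measures section offers three scores and does not say which of them, or which combination, enters it.

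**Working it through.** **1. Reproducing the plan's sample size.** Inputs from Sample size calculation: f(V) = .25, alpha = .05, k = 3 groups, m = 3 times, repeated measures MANOVA, group-by-time interaction. The G*Power formulation (Pillai) uses

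- s = min(k − 1, m − 1) = 2
- df1 = (k − 1)(m − 1) = 4
- df2 = s[N − k − (m − 1) + s] = 2(N − 3)
- noncentrality = N × s × f(V)²

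| N | df2 | Noncentrality | Power at .05 |
|---|---|---|---|
| 151 | 296 | 151 × 2 × .0625 = 18.875 | .950 |
| 98 | 190 | 98 × 2 × .0625 = 12.25 | .800 |

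Both stated totals are reproduced exactly, so the same method can be used to cost a correction.

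**2. Error rate across the two stated primary tests.** If they are independent, 1 − (1 − .05)² = 1 − .9025 = .0975. Under any dependence the rate cannot exceed .05 + .05 = .10.

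The document gives no correlation between the outcomes, so a range was assumed. The planned 4-df interaction F test was simulated with no effect on any outcome, 50 per group, within-person correlation .5 (assumed) and 20,000 runs.

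| Assumed correlation between outcomes | Two tests: at least one significant | Four tests: at least one significant |
|---|---|---|
| 0 | 9.6% | 18.5% |
| .3 | 9.9% | 17.3% |
| .5 | 9.5% | 16.2% |
| .7 | 8.2% | 14.0% |
| .9 | 6.9% | 9.9% |

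The simulation error is about √(.095 × .905 / 20,000) = .002 for the two-test column, so the first three of its entries do not differ from the exact 9.75% by more than noise.

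**3. The conditional four-test case.** If burnout were tested as three subscales beside detachment, the independent case would be 1 − .95⁴ = 1 − .8145 = .1855. The last column of the table covers correlated scores.

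**4. After correction.** Holm's procedure compares the smaller p-value with .05/2 = .025 and, if that succeeds, the larger with .05. It holds the family-wise rate at or below .05 under any correlation. At the first step, with independent tests, 1 − .975² = .0494.

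**5. Power at the first Holm step**, by the formula in step 1 with alpha = .025:

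| N | Power at .05 | Power at .025 | N needed at .025 for the original power |
|---|---|---|---|
| 151 | .950 | .914 | 172 |
| 98 | .800 | .712 | 116 |

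These are per-outcome figures for the test used in the sizing. Holm's power for either outcome is never below them.

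**The case against.** The strongest reply is that a significant interaction is not yet a claim. The stated hypothesis is that CBT exceeds MBSR and control, and group comparisons come only after a significant interaction and then with Bonferroni. In a simulation with no effects at all (50 per group, within-person correlation assumed .6, 10,000 runs), the chance that either outcome passed its interaction test and then showed CBT better than at least one comparator after the intervention or at follow-up was under 1%. This stands as a limit on wording: 9.75% is the rate for the primary interaction tests, not for the specific CBT hypothesis. It does not remove the point. The article also sets out to evaluate MBSR, and within-group change is part of its hypotheses, so other claims can follow from either interaction. The interaction tests are also what the trial is powered on.

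A second reply is that scoring of a published instrument is commonly left to the full protocol or SAP. That is fair for item-level detail and reverse-coding. It does not cover which of three dimensions, or what composite, is the primary outcome when the article itself counts a single test. Nor can the significance level be called a detail left open, because the article states both the level and where the correction applies.

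Several stronger readings are tempting but not supported:

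- **A false-positive rate near 19%.** This needs four independent primary tests. The article states two, and subscales of one instrument are unlikely to be independent.
- **Efficacy summed unreversed, cancelling exhaustion.** Nothing in the article suggests it.
- **A burnout score picked after seeing the data.** The article does not prevent this, but an unseen SAP may.
- **A 37% error rate among secondary outcomes** (1 − .95⁹ for nine null outcomes). The plan does say "Significant interaction effects will be followed-up with ANOVAs for each of the dependent variables", but the figure assumes independence, while the MANOVA is to be used only if those outcomes are moderately correlated. Correcting gated secondary tests is a matter of preference.

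**Conclusion.** The point holds for the two primary interaction tests. As planned, the chance of at least one false primary interaction is up to 9.75%, about 8 to 9.5% at outcome correlations of .7 to .5, and about 7% at .9, against the stated .05. This rests on three things: either outcome can succeed alone, neither intervention has any effect on either outcome, and the correlation is assumed because the document gives none. If both outcomes had to be significant there would be no inflation, but no such rule is stated.

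The single score entering the burnout ANOVA is not identified. Three subscale tests would put the rate at about 14% (correlation .7) to 18.5% (independence), but this is a conditional case and not what the plan states.

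The trial remains interpretable. The correction should be made before the data are analysed.

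**What to change.** 1. In the Burnout section, name one score as the primary burnout outcome and state its scoring direction. This could be exhaustion, or a composite of the three dimensions with efficacy reversed. List the remaining subscales as secondary.
2. In Effect evaluation, state that the two primary group-by-time interactions are tested with Holm's procedure at overall .05. The Bonferroni step for simple effects can stay as it is.
3. In Sample size calculation, restate power for the first Holm step: .914 at 151 and .712 at 98.

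The first two changes cost only wording. The third discloses a real loss: modest at the full sample, but nearly nine percentage points at the drop-out fallback (.800 − .712 = .088), which could no longer be described as having power .80. Keeping the original power would need 172 participants instead of 151 (21 more), or 116 instead of 98 as the fallback (18 more). Study design already provides for additional rounds of data collection if the target is not met, so the sponsor can either raise the target or accept and report the lower power.

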### Strengths and limitations

The proposed study, however, is not without its limitations. First, a more general limitation is related to the focus of the intervention. The intervention can be considered as an individual-focused intervention aimed at teaching employees how to better deal with demanding work conditions and, in turn, become more relaxed and more resilient. As the culture, norms, and practices in many organizations today encourage constant availability and extended work hours [92], some of the underlying causes of poor psychological detachment and ill-being thus will not be tackled. In order to deal with these organizational issues, organization-focused interventions that would result in meaningful changes in the work environment, lower levels of job demands, and increased resources (i.e., job re-design) should also be considered [15]. Moreover, multimodal interventions combining individual- and organization-focused elements should be sought after, as they are most likely to result in sustained beneficial effects for employee well-being [93]. Second, both the CBT and mindfulness interventions are based on a pre-defined set of online exercises and homework, which may undermine the participants’ need for autonomy. Previous studies have shown that workplace interventions should offer participants the opportunity to form their own intervention objectives and exercises during the intervention process [94]. Such a participative design is likely to facilitate intervention effects by being tailored to employees’ specific needs and preferences. Nevertheless, it should be considered that our online interventions provide a high degree of flexibility in terms of time and location of practicing mindfulness and carrying out the CBT exercises and homework. Third, the exercises and homework can take up a significant amount of time. Employees may eventually become less motivated or even fatigued by the added burden to their daily routines, which can attenuate the intervention effects, lead to non-adherence, or even drop-out. Selective drop-out in the CBT intervention group may be particularly problematic, as CBT homework may be perceived as more difficult than mindfulness exercises [33]. The online intervention design can also represent a potential factor of non-adherence and drop-out, as employees may feel less obliged to participate in the protocol than in face-to-face meetings. In line with previous interventions in the workplace context [95], several measures will be taken to avoid these complications. Participants will be briefed about the duration of each of the sessions and the overall intervention in an informed consent form. We will also stress the importance of participating in the study throughout the whole intervention. In-between sessions, participants will also receive e-mail reminders. Adherence will also be monitored by the online platform, which will additionally help to determine whether one of the groups is more compliant with the protocol than the other.

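### The primary repeated-measures ANOVA is complete-case by default, while the plan tolerates a 35% loss on power grounds alone and flags selective CBT drop-out without an analytic answer

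*Protocol article*

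**What the plan says.** Three places in the protocol article bear on this.

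- **Effect evaluation** fixes the primary model. The two main outcomes "will be analyzed with two separate two-way repeated measures analyses of variance (ANOVAs"), one model for each outcome. All three occasions, T1, T2 and T3, enter as levels of the time factor, and the allocated arm is the other factor. A significant interaction is followed by Bonferroni-adjusted simple effects. The software is also named: "The analyses will be carried out with SPSS [88] and Mplus [89"].
- **Sample size calculation** asks for 151 participants at power .95, described as the minimum to recruit. Attrition is then handled in one sentence: "In case of non-adherence and/or drop-out, the total sample size of 98 participants (approximately 33 participants per group) suffice" at power .80.
- **Strengths and limitations** states: "Selective drop-out in the CBT intervention group may be particularly problematic". The reason given is that CBT homework may seem harder than mindfulness exercises. The measures listed are briefing participants, stressing the importance of taking part, e-mail reminders and adherence monitoring by the platform.

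The article names no analysis population and no method for missing T2 or T3 values.

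**The concern.** A classical repeated-measures ANOVA with a three-level time factor needs a complete T1–T2–T3 record for each person. A participant who completes T1 and T2 but misses the three-month follow-up contributes nothing, not even to the pre–post comparison.

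Loss of up to a third of the sample is treated only as a loss of power. Power is one consequence; the other is that those left may no longer be comparable between arms. The protocol itself names a reason why loss could differ in CBT, the arm it hypothesises to be superior. Its planned measures may reduce drop-out, but they do nothing for the analysis once drop-out has occurred. At stake is whether the estimate for each primary outcome is still a randomised comparison.

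**Working it through.** **1. The plan's own figures.** Inputs from Sample size calculation: effect size f(V) = 0.25, two-sided error rate not applicable to an F test so simply α = 0.05, target power 0.95, three groups and three times. For the repeated-measures MANOVA interaction with s = 2: df1 = 4, df2 = 2(N − 3), λ = N × 2 × 0.25².

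- N = 151: df2 = 296, λ = 18.875, power 0.9500.
- N = 98: df2 = 190, λ = 12.25, power 0.8005.

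Both stated sizes reproduce.

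**2. The tolerated loss.** 1 − 98/151 = 35.1%. Keeping 151 complete cases at that loss would take 151/(1 − 0.351) = 233 randomised. That would restore power but leave any selection bias in place.

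**3. Possible size of the bias.** The protocol gives no drop-out rate, no correlation between times and no link between loss and outcome, so every input here is an assumption. There is no true effect. Scores are standard normal with correlation .6 between any two times, oriented so that higher is better. CBT loses 45%, with the log-odds of leaving rising by 1 per SD of worse score at the driving time. Control loses 30% at random, so its completers' mean is unbiased and any shift in CBT is the between-arm bias.

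The CBT completers' mean at the driving time shifts by +0.37 SD. At the other two times it shifts by .6 × 0.37 = +0.22 SD. Hence:

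| Loss in CBT driven by | T2 bias, raw mean | T2 − T1 bias | T3 − T1 bias |
|---|---|---|---|
| low T1 | +0.22 | 0.22 − 0.37 = −0.15 | −0.15 |
| low T2 | +0.37 | 0.37 − 0.22 = +0.15 | about 0 |
| low T3 | +0.22 | about 0 | +0.15 |
| high T2 (good responders leave) | −0.37 | −0.15 | about 0 |

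Variations:
- Equal 35% loss in both arms, selective only in CBT and driven by T2: T2 − T1 bias is still about +0.12 SD. Equal rates do not protect if the mechanism differs.
- Equal 35% loss with the same mechanism in both arms: bias about 0.
- Same mechanism in both arms, 45% against 30% loss, correlation .5, slope 0.5 to 1: T3 − T1 bias −0.03 to −0.06 SD if T1 drives loss, +0.04 to +0.07 SD if T3 does.
- Milder slope of 0.5 in CBT only, T2-driven, correlation .5 to .7: T2 − T1 bias +0.05 to +0.11 SD.

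**4. Type I error of the planned test.** With 50 randomised per arm and T2-driven loss as in the table, the group × time interaction rejects in about 8% of null trials with three groups (the other two arms losing 30% at random) and about 10% with CBT and control only, against a nominal 5%. At the milder slope it is about 5–7%.

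**5. What using all available data achieves.** If T2 drives the loss and everyone supplies T1 and T2, a regression of T3 on T1 and T2 applied to all has T3 bias below 0.01 SD. If T2 is missing as well and only T1 is available, the bias remains about +0.25 SD at T2 and +0.09 SD at T3. If loss depends on the unseen T3 value, using T1 and T2 does not remove the bias either.

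**The case against.** The best case for the plan has four parts.

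- **The rule is inferred.** The article never mentions listwise deletion, and imputation before the ANOVA is neither stated nor excluded. A condensed article may leave this to a fuller document. This stands as a limit on wording: complete-case is the method's default, not a declared rule. It does not remove the point, because the article does commit to a specific primary model, and that model copes poorly with the loss it foresees.
- **Selective drop-out is not predicted.** A reader might infer that the plan expects it. The text says only that it may be problematic, gives no rate, and attributes it to homework burden, not to poor response. The 35% covers non-adherence as well as drop-out and is a loss tolerated, not forecast; Study design also allows further recruitment rounds. All of this stands.
- **Non-adherers are not said to be excluded.** A reader might infer from the 98 that only adherers will be analysed. No section says so, and the objectives treat compliance and homework completion as possible moderators, which points to keeping partial adherers.
- **The error inflation is modest for the planned test.** An uncorrected comparison of raw T2 means would reject in about 32–33% under the step 3 scenario with T2-driven loss. That is not the plan's test: simple effects follow only a significant interaction and carry a Bonferroni correction. The relevant figure is about 8–10%, under the stronger slope.

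**Conclusion.** The point holds as a risk. The primary model is complete-case by default, the plan answers a loss of up to 35% with power alone, and it names possible selective loss from CBT without an analytic response. Bias arises if loss is related to outcome and differs between arms in rate or mechanism.

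A reader might go further and conclude that the comparison will be biased in favour of CBT. The protocol does not support that. Under the assumed inputs the T2-change bias runs from about −0.15 to +0.15 SD, and it is about zero when both arms lose people at the same rate by the same mechanism. These sizes rest on assumed rates, slope and correlation and are illustrations, not forecasts. Nor does a mixed model guarantee an unbiased result: it helps most where the data observed before drop-out explain the loss. It is still the better primary analysis, because it keeps everyone's observed data and the randomised groups. The change should be made before outcome data are examined.

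**What to change.** - Replace the two ANOVAs with a linear mixed model for repeated measures for each primary outcome: group × time, unstructured covariance, and T1 either as a covariate or with baseline means constrained equal across arms.
- Include all randomised participants in their allocated arm, with whatever data they have and whatever their adherence.
- Use the weekly detachment and burnout scores, already collected during the six weeks, as auxiliary information for missing T2 and T3. This matters most for people who leave before T2.
- Report the completers' analysis as secondary.
- Add a missing-not-at-random sensitivity analysis, for example one that shifts the unobserved CBT values over a stated range.
- Keep the 98-participant statement as a remark on power only, and say that it does not define who is analysed.

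Cost: revised analysis wording and slightly more modelling. SPSS and Mplus, the packages already named, can fit these models. No extra participants or data are needed.
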